### Participants

This study consists of prisoners within the PPZ from April 1, 2015 until August 31, 2020. The final sample will be exhaustive. All inmates within this timeframe will be included in this study and there will be no random selection. Only in documented cases wherein a prisoner allegedly refuses to participate in health-related activities, he or she will be excluded from the study and his or her data will not be analyzed. Otherwise, there are no exclusion criteria. Extrapolating from current numbers (approximately 850 prisoners per month × 64 months), it is expected that the final database will contain data from approximately 50,000 to 60,000 prisoners.

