**Methods:**

Demographic and health-related data such as age, sex, country of origin, duration of imprisonment, medication (including the drug name, brand, dosage, and release), and medical history (including the International Classification of Diseases-10 codes [German modification] for all diagnoses and external results that are part of the medical history in the prison) have been deposited in a central register over a span of 5 years (January 2015 to August 2020). The final cohort is expected to comprise approximately 50,000 to 60,000 prisoners from the Police Prison Zurich, Switzerland.

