### Study Objectives

The primary objective is to establish a central database to assess the prevalence of diseases (ie, International Classification of Diseases [ICD]-10 codes [German modification]) among prisoners. The secondary objectives are (1) to compare the 2015 versus 2020 disease prevalence among inmates against a representative sample from the local resident population, (2) to assess longitudinal changes in disease prevalence from 2015 to 2020 by using cross-sectional medical records from all inmates at the PPZ, and (3) to identify unrecognized health problems to formulate models for successful public health strategies. Achieving these objectives can result in new insights into public health and in the construction of a valuable database of information regarding the health of inmates and refugees in Swiss prisons, thereby enabling future interventions in this vulnerable population.

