### Study Site

The health registry is based at the PPZ ([name]). In this prison, all inmates of the Canton of Zurich are detained for up to a maximum of 7 days. Thereafter, prisoners are transferred to any of the following systems: (1) pretrial detention, (2) serving a particular prison sentence in a long-term facility, (3) anticipatory execution of sentence, or (4) subjection to coercive measures based on Aliens Act. The PPZ is the only central police prison in the Canton of Zurich serving a population of 1,520,968 (as of December 31, 2018), which is the most populous canton in the country. This prison has approximately 10,000 to 12,000 inmates yearly, of which about a third require medical attention (based on historical data from the PPZ/not published). The entire spectrum of medical attention needed to meet inmates’ medical needs is covered within the PPZ, such as general internal medicine (eg, asthma), traumatic injuries, psychiatric emergencies, and infectious diseases (eg, HIV).

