### Outcomes

The primary outcome measure will be disease prevalence by using cross-sectional data from prisoner’s medical records (ie, using the ICD-10 codes [German modification]) from 2015 to 2020. Secondary outcome measures include the following: (1) A comparison of disease prevalence (ICD-10 codes [German modification]) of the inmates at the PPZ to that of a representative sample from the local resident population by using cross-sectional medical records from all inmates at the PPZ from 2015 to 2020 and (2) longitudinal changes in disease prevalence (ICD-10 codes [German modification]) from 2015 to 2020 by using cross-sectional medical records from all inmates at the PPZ.

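### The accrual window has two start dates and a month count that fits neither, and 2015 and 2020 cover different calendar months, so the 2015-versus-2020 contrast mixes time with season.

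*Protocol article*

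**What the plan says.** The Participants section sets the cohort: "This study consists of prisoners within the PPZ from April 1, 2015 until August 31, 2020". It describes the sample as exhaustive for that period, so the start date works as an inclusion criterion. The Methods paragraph of the Abstract says that data "have been deposited in a central register over a span of 5 years (January 2015 to August 2020".

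Participants then projects the database size from "approximately 850 prisoners per month × 64 months" and concludes that "it is expected that the final database will contain data from approximately 50,000 to 60,000 prisoners". Study Site gives a second rate: "This prison has approximately 10,000 to 12,000 inmates yearly".

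Two secondary aims use the end years or the span between them:
- Objective 1 (Study Objectives) is "to compare the 2015 versus 2020 disease prevalence among inmates against a representative sample from the local resident population".
- The second secondary outcome (Outcomes) is "longitudinal changes in disease prevalence (ICD-10 codes [German modification]) from 2015 to 2020". The first secondary outcome also refers to records from 2015 to 2020 and does not name a two-year contrast.

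Statistical Considerations lists the potential confounders as age, sex and nationality, and plans a mixed model for the longitudinal data with random effects for nationality. No section names month or season, or restricts the contrast to matching months.

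**The concern.** A reader cannot tell whether detentions from January to March 2015 belong to the cohort. At 850 per month that is 3 × 850 = 2,550 records.

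The window also fixes which months stand for each year in objective 1. Study Site caps stays at 7 days and Study Design plans no follow-up, so each record is a snapshot. The month of detention therefore influences whether a seasonal or acute condition is seen. Study Questions asks about infectious diseases, pneumonia among them, and about the balance of acute and chronic conditions. The Hypothesis section attributes change over these years to geopolitical events. If the two years cover different months, a seasonal difference, or a seasonal shift in who is arrested, could be read as support for that hypothesis.

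**Working it through.** **The plan's own figure.** 850 × 64 = 54,400, inside 50,000 to 60,000. The size reproduces.

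**Month counts, inclusive of both end months.**
- Participants dates: 9 (2015) + 48 (2016 to 2019) + 8 (2020) = 65; 65 × 850 = 55,250, which is 1.6% above 54,400.
- Abstract dates: 12 + 48 + 8 = 68; 68 × 850 = 57,800, which is 6.3% above 54,400.
- 64 results only if April 2015 is subtracted from August 2020 without counting both end months.

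All three sizes lie inside the stated range.

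**Calendar coverage.**

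| Start | 2015 months | 2020 months | Common | Only in 2015 | Only in 2020 |
|---|---|---|---|---|---|
| 1 April 2015 | Apr–Dec (9) | Jan–Aug (8) | Apr–Aug (5) | Sep–Dec (4/9 = 44%) | Jan–Mar (3/8 = 37.5%) |
| January 2015 | Jan–Dec (12) | Jan–Aug (8) | Jan–Aug (8) | Sep–Dec (4/12 = 33%) | none |

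At a constant 850 per month, the April start gives 9 × 850 = 7,650 records for 2015 and 8 × 850 = 6,800 for 2020.

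**Illustration of the distortion.** Assume that prevalence is r times higher in the peak months, with equal monthly intake and no true change. If s is the share of a year's covered months that are peak months, the spurious ratio is

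(1 + (r − 1)·s₂₀₂₀) / (1 + (r − 1)·s₂₀₁₅).

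With r = 2:

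| Assumed peak | April start: s₂₀₁₅, s₂₀₂₀ | Ratio, April start | Ratio, January start |
|---|---|---|---|
| Oct–Mar | 3/9, 3/8 | 1.375/1.333 = 1.03 | 1.375/1.50 = 0.92 |
| Dec–Feb | 1/9, 2/8 | 1.25/1.111 = 1.125 | 1.25/1.25 = 1.00 |
| Jan–Mar | 0/9, 3/8 | 1.375/1 = 1.375 | 1.375/1.25 = 1.10 |
| Sep–Dec | 4/9, 0/8 | 1/1.444 = 0.69 | 1/1.333 = 0.75 |

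With no seasonal excess (r = 1) every ratio is 1.

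**Chance of a false finding.** This uses a two-sided test at 0.05 with 7,650 and 6,800 records. At an assumed 2% off-season prevalence and the April start, the chance of declaring a change in the spurious direction is about 5%, 20%, 84% and 93% for the four peaks in the order of the table. The result depends strongly on prevalence. For the December–February peak it is about 12% at a 1% base, 20% at 2% and 73% at 10%.

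**The case against.** The strongest reply has five parts.

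- **The arithmetic slip is harmless.** This stands. 54,400, 55,250 and 57,800 all fit the stated range, and the five-year label is a rounded description, not a third window. A reader might apply the 10,000 to 12,000 yearly intake to 65 months, get about 54,200 to 65,000, and call the expected size wrong. But 850 × 12 = 10,200 already agrees with that intake, so the projection is sound.
- **Objective 1 compares inmates with residents.** If the resident data cover the same months, season would affect both sides. The documents give no months for the resident data, so this reply is possible but unsupported.
- **The end years are not the only plan.** This stands. Objective 2 and the mixed model use the whole span, so it would be wrong to say that all inference on change rests on 2020. That model still names no month term.
- **The distortion may be small.** This stands in part. It is about 3% for a broad October–March peak and nil for stable diagnoses. A reader might quote the 73% as typical, but it needs 10% off-season and 20% winter prevalence among all inmates. Study Site says that about a third need medical attention, so 20% would be roughly 60% of those, which does not suit pneumonia.
- **Seasonal terms belong in an analysis plan, which is not shown.** Such a plan might supply them. However, the article itself fixes the window, the contrast and the named confounders, and its two windows disagree. Its silence on the pandemic is an omission of the kind an analysis plan can cover, and this point does not rest on it.

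**Conclusion.** The window is wrong as written: there are two start dates, and the count of 64 fits neither 65 nor 68 months. This does not affect the expected size.

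The consequence for the analysis is that the 2015-versus-2020 contrast compares partly different months, with no seasonal adjustment named. A reader might infer that settling on January 2015 would remove the problem. It would not in general, because 2020 still ends in August. A January start removes the bias for a December–February peak, but it makes an October–March peak worse (0.92 against 1.03) and leaves 0.75 for September–December.

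The size is unknown. Under an assumed twofold excess and the April start, the ratio spans about 0.69 to 1.375. The direction depends on the peak months, and non-seasonal diagnoses are unaffected unless the arrest mix itself shifts with season, which the documents do not quantify. These figures rest on equal monthly intake and assumed seasonal patterns.

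The primary objective is not invalidated, and the point touches a secondary contrast that the recorded data can repair. It should be fixed, but it is not a fatal flaw.

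**What to change.** 1. State one start date in the Abstract and in Participants, and correct the month count. If 1 April 2015 stands, write 65 × 850 = 55,250; the range of 50,000 to 60,000 can remain.
2. Make the 2015-versus-2020 contrast on the months common to both years (April to August under the Participants dates, January to August under a January start), or add calendar-month terms to the planned longitudinal model fitted to all months.
3. State that the resident comparator covers the same months.
4. Word objective 1 and the first secondary outcome consistently, saying whether the comparison with residents is made separately for 2015 and 2020 or over the whole period.

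**Cost.** No new data are needed, because Table 1 already records the date of imprisonment. Restricting to April–August leaves about 5 × 850 = 4,250 records per year instead of 7,650 and 6,800. At equal prevalence the standard error of the difference grows by √[(2/4,250) / (1/7,650 + 1/6,800)] = 1.30, about 30%. The all-months model largely recovers that loss.

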### Police Prison Zurich

Prison facilities are required to ensure adequate health care in both the somatic and psychiatric fields. The University Hospital Zurich has taken over the responsibility for providing somatic and psychiatric care to the Police Prison Zurich (PPZ) inmates. The PPZ is the largest inmate correctional facility in Switzerland, and approximately 10,000 to 12,000 prisoners are admitted per year. Data from the Federal Statistical Office in Switzerland indicate that inmates held for pretrial detention are predominantly young and male, and approximately 75% are non-Swiss nationals (Figure 1) [12]. Anecdotal evidence suggests that a large proportion of inmates (eg, refugees) have reported previously using drugs that were prescribed for off-label purposes. One example is the prevalent purchase of the substance *pregabalin* via web-based pharmacies [14]. Other examples include the underestimated usage of recreational drugs (eg, clonazepam) and other NPS [15]. Most of these drugs have potentially substantive health consequences, mainly attributed to their high potential for addiction and adverse effects. Furthermore, little information has been established on how recent refugee patterns may have affected the health conditions of the inmates in recent years.

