## Methods

### Study Design

This is an observational study with a population-based cross-sectional baseline measurement and no prospective follow-up.

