### Data Protection

In this registry, anonymized health data will be analyzed and stored. Other sensitive data, particularly, religious, political, social security, or administrative data will not be included as part of this study. The anonymized data sets generated or analyzed during this study will be available upon request from TG. Data are handled according to the Schengen Data Protection Act.

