### Statistical Considerations

Statistical analyses will be conducted by the study team in consultation with senior statisticians. For baseline analyses, means or medians will be reported according to the distribution of the continuous variable. Proportions will be reported for categorical variables. For hypothesis testing, a two-sided *t* test for normally distributed continuous variables and nonparametric tests for nonnormally distributed continuous variables will be conducted; chi-square testing will be used for categorical variables. Linear or logistic regression models with or without adjustment for potential confounders (ie, age, sex, nationality) will be used when appropriate. Regression analysis estimates will be reported using 95% confidence intervals, and a two-sided *P* value of <.05 will be considered statistically significant for all reported tests. For the longitudinal data, a generalized linear mixed model with random effects (accounting for the nationality of the prisoner during the refugee crisis) will be used when appropriate. Statistical analyses will be performed using STATA Version 16 (StataCorp LP).

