## Discussion

This health registry is designed to provide new public health insights into a group of vulnerable patients. The implementation of the study protocol promises to allow for the identification of specific health problems to help prepare successful public health strategies to meet these challenges. To gain a representative sample from the Canton of Zurich inmate population, this study required a high enrollment. Inmates at the PPZ usually spend a minimum of 1 day to a maximum of 7 days in the facility; they are internationally mobile, often unable to speak German, and have no contact details provided. Gaining informed consent from each prisoner is a disproportionately large expenditure. In this observational study, we assume that the expected increase in knowledge will benefit future inmates and thus, outweigh the disadvantages associated with privacy concerns. Moreover, given these operational challenges, any large-scale study on the prisoner population will likely need to be conducted without receiving individualized informed written consent. Thus, in accordance with the Swiss Human Research Act Article 34, the need to obtain informed consent is waived for this study, and data collected from all prisoners will be gathered. Only in case of documented alleged refusal to participate in health-related activities, data from the prisoner will not be included in this study.

Currently, no similar observational studies on Swiss inmates are available. Data from the United States and European registries indicate that prisoners are sicker when compared with their counterparts in a free society [2-4]. However, these data are limited to a certain location and time and they do not investigate changes over time within a certain cohort. Preliminary studies suggest that illicit drugs and especially NPS are a growing problem in European prisons, but only limited data from European prisons are available [7,8]. This study will be able to draw conclusions on these issues based on a 5-year representative sample of approximately 50,000 to 60,000 prisoners from the PPZ. Thus, this study will add valid evidence to the current health status of prisoners, and findings can be used to promote healthy behaviors (eg, future intervention studies) or policy change for this population.

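### The expected 50,000 to 60,000 prisoners is a count of admissions, and the article lists neither a person key nor any allowance for repeat stays

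*Protocol article*

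**What the plan says.** The Participants section gives the expected size in one sentence: "Extrapolating from current numbers (approximately 850 prisoners per month × 64 months), it is expected that the final database will contain data from" 50,000 to 60,000 prisoners. The Abstract and the Discussion repeat the total as prisoners, and the Discussion calls it a representative sample. The section on the Police Prison Zurich describes the same flow as follows: "approximately 10,000 to 12,000 prisoners are admitted per year". Study Site limits a stay to 7 days and describes the facility as the canton's sole central police prison.

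Everyone held between 1 April 2015 and 31 August 2020 is included, and the only exclusion is documented refusal. No rule covers a person who is held more than once. Data Collection and Management says the case report form was built on Tables 1 and 2 and that these cover all variables. Table 1 has one date and one length of imprisonment, and neither table lists a person identifier. Data Protection adds that "anonymized health data will be analyzed and stored".

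Statistical Considerations names t tests, nonparametric tests, chi-square tests, and linear or logistic regression. For the longitudinal data it names a "generalized linear mixed model with random effects (accounting for the nationality of the prisoner during the refugee crisis"). Outcomes defines the primary outcome as disease prevalence over 2015 to 2020 and does not say whether the denominator is people or stays.

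**The concern.** A monthly inflow summed over five years gives people only if nobody comes back. In a short-stay facility that serves a whole canton, some return is to be expected. Three things depend on this.

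- **The stated size.** The number of distinct people may be well below the number announced.
- **Precision.** Chi-square, t and ordinary regression analyses treat records as independent. Two stays by one person tend to carry the same chronic diagnoses, so an interval pooled over all stays would be too narrow. A random effect for nationality does not capture this.
- **The quantity estimated.** Prevalence per admission gives frequent returners more weight. The study asks in particular about psychiatric disease and substance abuse. If affected people return more often, prevalence per admission exceeds prevalence per person. If the insurer's comparison cohort counts people, the two sides of that comparison would also have different units.

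**Working it through.** 1. **The plan's own figure.** 850 × 64 = 54,400, inside the stated 50,000 to 60,000. April 2015 to August 2020 is 9 + 48 + 8 = 65 months, which gives 850 × 65 = 55,250. The Abstract's January 2015 start gives 68 months and 57,800. All three lie in the stated range, so the month count is not the issue.

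2. **What is being counted.** 850 × 12 = 10,200 per year, which matches the 10,000 to 12,000 described as yearly admissions. With stays of at most 7 days, the monthly figure is turnover. The product is therefore a number of admissions.

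3. **From admissions to people.** People = admissions / mean admissions per person. The lower bound of 50,000 people fails once the mean exceeds 54,400/50,000 = 1.088 (55,250/50,000 = 1.105 with 65 months). The documents give no readmission rate. For assumed means:
   - 1.1: 54,400/1.1 = 49,455 people
   - 1.25: 43,520
   - 1.5: 36,267
   - 2.0: 27,200

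4. **Interval width for a pooled prevalence (illustration only).** With m admissions per person and within-person correlation ρ of the recorded diagnosis, the design effect is DE = 1 + (E[m²]/E[m] − 1) × ρ. The correct interval is √DE times the naive one. The return patterns and ρ are assumed.

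| Assumed pattern | E[m] | E[m²]/E[m] | DE at ρ = 0.5 | DE at ρ = 0.9 | Width ratio |
|---|---|---|---|---|---|
| 5% of people have 2 stays | 1.05 | 1.15/1.05 = 1.10 | 1.05 | 1.09 | 1.02 to 1.04 |
| 10% have 3 stays | 1.20 | 1.80/1.20 = 1.50 | 1.25 | 1.45 | 1.12 to 1.20 |
| 20% have 5 stays | 1.80 | 5.80/1.80 = 3.22 | 2.11 | 3.00 | 1.45 to 1.73 |

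   In absolute terms, at 20% prevalence and 54,400 records the naive half-width is 1.96 × √(0.2 × 0.8/54,400) = 0.34 percentage points. At DE = 3.00 it is 0.34 × 1.73 = 0.58 points.

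5. **Weighting (illustration only).** Suppose 10% of people have 3 stays and a prevalence of 30%, and the others have one stay and 10%. Per person: 0.9 × 0.10 + 0.1 × 0.30 = 12.0%. Per admission: (0.9 × 0.10 + 0.1 × 3 × 0.30)/1.2 = 15.0%. If returners have the same prevalence as others, the two figures agree.

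6. **2015 versus 2020.** The variance of the difference is V₁ + V₂ − 2 Cov. Repeat stays within a year raise V₁ and V₂, which makes a naive test too liberal. People present in both years raise the covariance, which makes it too conservative. Without data on returns the net direction is open.

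**The case against.** The strongest reply is that this is a condensed article. Handling of repeat stays, record keys and standard errors is often left to the full protocol or analysis plan. A record key is not a health parameter, so its absence from the tables is weak evidence. Matching the registry to the jurisdiction's database, as Quality Control requires, needs some link at record level. Prevalence per admission is also a legitimate target for a prison health service. With a sample this large, the absolute loss of precision is small, and no power calculation depends on the count.

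Much of this stands, and it rules out several stronger readings that a reader might infer:

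- That the plan analyses readmissions as different people. It never says so; it only leaves the matter without a rule. Anonymisation does not by itself show that repeat stays were never linked.
- That a particular false-positive rate or a particular inflation of prevalence follows. Such figures rest wholly on assumed return patterns and correlations. Only about a third of inmates are said to need medical attention, so a diagnosis recorded at one stay may be missing at another, which lowers the correlation. A rate derived for a pooled estimate also does not carry over to 2015 versus 2020 (step 6).
- That the Discussion promises change within individuals. The remark that "they do not investigate changes over time within a certain cohort" describes other registries. Study Design states a "population-based cross-sectional baseline measurement and no prospective follow-up", and the objectives say that change is assessed from cross-sectional records.

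The reply does not remove the rest. The article itself labels an admission flow as prisoners. It presents its variable list as complete, and it names a random effect at the nationality level only. A later analysis plan cannot cluster on a key that was not recorded. If admissions are the intended unit, that is defensible, but it has to be stated, and repeat stays still break independence.

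**Conclusion.** The point holds in limited form. The mislabelled count is the firm part: 54,400 is a number of admissions, and 50,000 distinct prisoners is not reached if the mean exceeds 1.088 admissions per person. The analysis part is an inference from the listed variables, tests and models. Followed as written, they leave the denominator of the primary outcome undefined and make pooled intervals too narrow. The narrowing requires that some people return and that their recorded diagnoses are positively correlated across stays. A gap between prevalence per admission and per person requires that returners differ in disease from one-time inmates. Neither effect can be sized from the documents. Under the assumed patterns, pooled intervals should be 1.02 to 1.73 times as wide, and one weighting example moves 12% to 15%. In a database this large, the weighting question matters more than interval width, because sample size does not cure it.

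**What to change.** - Restate 50,000 to 60,000 as admissions wherever it appears.
- Add a coded person key at data entry, assigned before anonymisation, so that stays by one person can be linked without identifying that person. Source documents are filed by prisoner, and the registry is already to be matched with the jurisdiction's data, so this should be feasible. Report both admissions and distinct people.
- Define the denominator of the primary prevalence. For the pooled 2015 to 2020 estimate, count each person once, for example at the first admission in the period. For a year-specific estimate, use the first admission in that year. First admission per calendar year would not be enough for the pooled estimate, because one person could still enter it up to six times.
- In any analysis that includes repeat stays, use person-clustered standard errors or a person random intercept. This includes 2015 versus 2020, where one person may appear in both years.

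The cost is a smaller stated number of prisoners, somewhat wider intervals and a little extra data entry.
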